## Abstract

**Background:**

Acute kidney replacement therapy (KRT) is delivered to acutely ill patients to support organ function and life in the Intensive Care Unit (ICU). Implementing standardized acute KRT pathways can ensure its safe and effective management. At present, there is no standardized approach to the management of acute KRT in Alberta ICUs.

**Methods:**

Dialyzing Wisely is a registry embedded, stepped-wedge, interrupted time-series evaluation of the implementation of a standardized, stakeholder-informed, and evidence-based acute KRT pathway into Alberta ICUs. The acute KRT pathway will consist of two distinct phases. First, we will implement routine monitoring of evidence-informed key performance indicators (KPIs) of acute KRT. Second, we will provide prescriber and program reports for acute KRT initiation patterns. After the implementation of both phases of the pathway, we will evaluate acute KRT performance quarterly and implement a customized suite of interventions aimed at improving performance. We will compare this with baseline and evaluate iterative post implementation effects of the care pathway.

**Discussion:**

Dialyzing Wisely will implement, monitor, and report a suite of KPIs of acute KRT, coupled with a care pathway that will transform the quality of acute KRT across ICUs in Alberta. This program will provide a framework for scaling evidence-informed approaches to monitoring and management of acute KRT in other jurisdictions. We anticipate improvements in acute KRT performance, decreased healthcare system costs and improved patient quality of life by decreasing patient dependence on maintenance dialysis.

**Trial registration:**

Clinicaltrials.gov, NCT05186636. Registered 11, January, 2022.

**Supplementary Information:**

The online version contains supplementary material available at 10.1186/s12882-022-02990-6.

## Background

Acute kidney replacement therapy (KRT) is a core life support technology used in approximately 10–12% of critically ill patients [1]. It is generally used to support patients with overt kidney failure or as part of a broader strategy for multi-organ support in ICU settings, along with mechanical ventilation and vasoactive medications. Its utilization has expanded, with recent estimates showing growth of more than 10% per year [2, 3]. Acute KRT in the ICU can be delivered intermittently (i.e., intermittent kidney replacement therapy [IKRT]) or continuously (i.e., continuous kidney replacement therapy [CKRT]) depending on the available technology.

### Acute KRT in Alberta

In 2019, acute KRT was initiated in 1278 patients across 18 adult ICUs in Alberta, which represents 5–8% of our critically ill population. This coincides with 3278 KRT patient-days of continuous KRT and 398 intermittent KRT patient-days with estimated direct healthcare costs of $764–865 per day and $528 per day, respectively [3, 4]. Non-adherence to evidence-based practice may have led to an additional 56 patients per year with new end stage kidney disease (ESKD) [5]. These survivors of critical illness complicated by severe AKI, who are now receiving maintenance dialysis after hospital discharge, have attributable healthcare costs exceeding $100,000 annually per patient [6, 7]. These costs do not include associated travel and lost work time costs as well as significant impairments in the quality of lives of these patients. Strategies are needed to standardize and reduce variations in care, improve patient centered outcomes, improve health system efficiencies and reduce patient and health care system costs.

### Current acute KRT practices are not standardized or monitored in Alberta

Presently in Alberta, the provision of acute KRT occurs without routine capture and reporting of performance indicators, and only the number of patients and patient-days receiving acute KRT are routinely reported [8]. Without mechanisms in place to better monitor this therapy, healthcare professionals cannot appreciate whether the therapy they provide aligns with current evidence and best practices and whether adjustments can be made to their practice to improve delivery of KRT [9]. This in turn, contributes to suboptimal, less effective, and potentially costlier provision of acute KRT through systemic inefficiencies, increased resource use, and higher healthcare professional workload for potentially lower value therapy.

### New evidence-based care practices are not always integrated into routine care

Care practices evolve as new evidence on best practice emerges. However, it is generally recognized that in the absence of targeted strategies, there is a delayed uptake of evidence into practice by at least 5–10 years [10]. Utilizing the principles of a learning health care system in which 1) knowledge gaps and variations in practice are identified; 2) clinical research is integrated into routine bedside care to address knowledge gaps; and 3) results are then seamlessly implemented into practice; would significantly decrease the knowledge to action gaps in the integration of new evidence-based practices into current acute KRT [11].

#### Monitoring of KRT practices

Evidence shows that monitoring and reporting of KPIs is an important aspect of any high performing acute KRT program [12]. Previous work by our study team has identified, validated and prioritized KPIs for acute KRT care [1, 2]. In addition, others have shown that initiatives such as: the implementation of KPIs through a quality dashboard to measure adherence to KRT standards; establishment of evidence-informed benchmarks; enhancement of documentation templates and acute KRT provider education; and integration of an evidence-based quality improvement system to support the management of KRT, have been successful in improving the quality of KRT delivery and establishing infrastructure to ensure ongoing sustainability of quality initiatives [13–15].

#### Time of KRT initiation

The STARRT-AKI trial found that standard initiation of acute KRT was not associated with increased mortality. However, accelerated initiation was found to lead to a higher occurrence of adverse events and a 74% relative increase in risk of failure to recover kidney function and remain on maintenance KRT at 90-days when compared to the standard delayed initiation strategy [5]. While these findings were published in 2020, there has been no formal process through which to integrate them into clinical practice in Alberta ICUs.

The implementation of the Dialyzing Wisely evidence-based care pathway would provide a standardize means of integrating new and evolving evidence-informed best care practices. In addition, practitioners would have a standard mechanism through which to improve practice utilizing strategies such as audit and feedback, benchmarking and interactive peer group learning.

## Objectives

The primary objective of this project is to implement and evaluate a multifaceted evidence-informed care pathway into acute KRT programs in Alberta ICUs (Fig. 1).

**Fig. 1 Fig1:**
[figure not shown]
Care Pathway for Dialyzing Wisely

### Research questions

Can we develop and implement a standardized framework to be implemented in all acute KRT programs?Will monitoring the performance of our acute KRT delivery by means of evidence-based KPIs result in improved performance and a decrease in acute KRT program costs?Can we rapidly implement the findings of novel programs of research into clinical practice to improve patient-centered outcomes and decrease both short and long-term healthcare costs?

## Methods/design

Dialyzing Wisely is a multi-centre, registry embedded, stepped-wedged, interrupted time-series evaluation of the implementation of an evidence-based and best practice acute KRT pathway in the 15 adult general and cardiac ICUs and 3 pediatric general and cardiac ICUs in Alberta that provide acute KRT (Table 1). This implementation plan will follow the principles of the Learning Health System Knowledge to Action Framework (Fig. 2) [16].

**Table 1 Tab1:** Alberta ICUs Delivering KRT

Site	City/Zone^**a**^	ICU Type	Hospital Type	Beds
University of Alberta Hospital General Systems ICU	Edmonton	Mixed	Academic	32
Mazankowski Alberta Heart Institute Cardiovascular ICU	Edmonton	Cardiac surgery	Academic	24
Mazankowski Alberta Heart Institute Cardiac ICU	Edmonton	Cardiac	Academic	8
Royal Alexandra Hospital ICU	Edmonton	Mixed	Academic	25
Grey Nuns Hospital ICU	Edmonton	Mixed	Community	8
Misericordia Hospital	Edmonton	Mixed	Community	10
Sturgeon Hospital ICU	Edmonton	Mixed	Community	5
Stollery Children’s Hospital Pediatric ICU	Edmonton	Mixed	Academic	16
Stollery Children’s Hospital Pediatric Cardiac ICU	Edmonton	Cardiac	Academic	16
Foothills Medical Centre ICU	Calgary	Mixed	Academic	28
Foothills Medical Centre Cardiovascular ICU	Calgary	Cardiac surgery	Academic	16
Foothills Medical Centre Cardiac ICU	Calgary	Cardiac	Academic	18
Peter Lougheed Centre ICU	Calgary	Mixed	Academic	18
Rockyview General Hospital ICU	Calgary	Mixed	Community	10
South Health Campus ICU	Calgary	Mixed	Community	10
Alberta Children’s Hospital Pediatric ICU/PCICU	Calgary	Mixed	Academic	15
Red Deer Regional Hospital ICU	Red Deer/Central	Mixed	Regional	12
Chinook Regional Hospital ICU	Lethbridge/South	Mixed	Regional	7

Edmonton zone provides acute KRT to North Zone patients as there are no KRT programs currently operating in North Zone ICU

^a^Alberta Health Service (AHS) is organized into five geographic zones: North (pop. 480,924), Edmonton (pop. 1,422,009), Central (pop. 476,6774), Calgary (pop. 1,710,560) and South (pop. 311,514) https://www.albertahealthservices.ca/assets/about/publications/ahs-ar-2020/zones.html

**Fig. 2 Fig2:**
[figure not shown]
Outline of learning health system knowledge to action framework. The healthcare system data are used to set local priorities for improvement. Data on priority problems and potential contributors help find the evidence based solutions to improve local health systems (data to knowledge). Using evidence based knowledge, this will inform local quality improvement and implementation science guided efforts (knowledge to performance). Finally, the continuous monitoring of local KPIs and practices will develop practice based knowledge while revealing future opportunities for quality improvement (performance to data). Adapted from Kilbourne et al. [16]

Dialyzing Wisely will utilize a structure-process-outcome framework for quality assessment by implementing a standardized framework to each acute KRT program (Fig. 3) [17, 18]. Each participating ICU will be structured to be led by a team with expertise in KRT (e.g., physician, educator, registered nurse, administrator) who will undergo and further disseminate targeted education strategies prior and during the intervention. Each ICU will receive quarterly performance reports on a minimum suite of essential KPIs tailored to their unit’s specific practice. Through this feedback the team members will work on adjusting and improving KRT practices that do not meet KPI benchmarks. Further, acute KRT prescribers will receive individualized reports outlining their prescription practices and their alignment with best evidence. Follow up with individual ICUs and practitioners will occur to better understand and evaluate prescribing practices. After completion of the intervention period, the impact of the intervention will be measured through select clinical and economic outcome measures (e.g., mortality, lengths of stay, KRT utilization and renal recovery). At this time, using our partners (outlined below) we will transition ownership to local stakeholders.

**Fig. 3 Fig3:**
[figure not shown]
Outline of Structure-Process-Outcome framework. The framework of elements which constitute each standardized acute dialysis program is depicted above. While themes remain consistent between programs, each program may use specific elements which work best within their own processes

The SPIRIT checklist is available as an Additional File.

### Trial oversight

Dialyzing Wisely will be governed by an Executive Committee. The Executive Committee will be comprised of Leads from 4 participating Strategic Clinical Networks (SCNs) (Critical Care, Medicine (Kidney Health Section), Cardiovascular Health and Stroke, and Maternal, Newborn, Child and Youth). SCNs are province-wide integrated teams that collaboratively identify and solve challenges within their specific area of health. SCN membership includes clinicians, patients, operational leaders, researchers, community and industry partners and other stakeholders [19].

The Executive Committee will be supported by an International Advisory Panel. This panel will be made up of critical care nephrology experts with a specific interest in quality and safety for acute KRT. The International Advisory Panel will provide a high-level review of program performance and will provide unbiased recommendations to ensure ongoing advancement and program success.

The program will also have a Steering Committee with representation from all stakeholder groups (i.e., physicians, nurses, educators, administrators, operational leads, epidemiologists, health economists, informatics specialists and patient-partners). This Steering Committee will review KPI reports and study developments to ensure ongoing appropriate program advancement and oversight.

Finally, key stakeholders have been identified at each individual study site to operationalize and champion the implementation of the acute KRT pathway and enact change. We will also include provincial organizations to facilitate our audit and feedback process and transition ownership of the program to local sites. This will include members listed above as well as the Alberta Medical Association Physician Learning Program (PLP).

All aspects of the governance will be overseen by the program manager, and facilitated by the research assistant. Key reporting and educational messaging will be delivered by Clinical Practice Leads with expertise in knowledge translation strategies (Fig. 4).

**Fig. 4 Fig4:**
[figure not shown]
Project governance and roles structure. ^*^Stakeholders will fill the role of Leadership and Educational leads for each Acute Dialysis program, fulfilling the Structure KPI Requirements in Dialyzing Wisely. All project committees will be supported by the Program Manager and Research Assistant. Key reporting and educational messaging will be facilitated by Knowledge Translation Specialists

### Population and eligibility

The inclusion criteria will be critically ill patients (i.e., adults and children) receiving acute KRT as part of their routine ICU care. No exclusion criteria will be applied.

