### Interventions, duration and frequency of follow-up

The acute KRT pathway will consist of two specific interventions:Monitoring, reporting and audit of acute KRT KPIs.Provision of individualized prescriber and program reports for acute KRT initiation patterns.

The acute KRT care pathway will be implemented in a stepwise fashion with a pilot followed by randomized stepped wedge roll out at centres across Alberta over the subsequent 21 months. Roll out of ICUs will be performed in clusters and will coincide with individual site activation of a novel, province-wide electronic provincial clinical information system (CIS), Connect Care (EPIC, Verona WI).

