#### Prescriber reporting

An ICU-specific prescriber and program report will be provided to each prescriber and ICU on a quarterly basis. The report will include: 1) the number of acute KRT initiations, 2) acute KRT initiations based on conventional indications (i.e., hyperkalemia, acidosis, metabolic status, oxygenation status and cumulative fluid status) termed ‘appropriate initiations’, 3) general guidelines of KRT initiation criteria as per STARRT-AKI standard initiation arm protocol. (Table 2) [5] These will be benchmarked against prescriber patterns from providers in the same ICU, as well as similar ICUs across Alberta.

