### Data management

Effects of prescriber and acute KRT program patterns in the initiation of acute KRT will be determined by monitoring resource use associated with initiation of KRT at both a program level and healthcare system level. This will be done by determining first the units of each resource and then by assigning costs to each unit. At the program level we will capture the number of acute KRT initiations as well as total patient-days of acute KRT per specific modality (i.e., intermittent or continuous). These acute KRT initiations will also be adjusted for severity of illness to enable translation across units with varying case-mix, acuity and workload. Acute KRT disposable costs will include KRT filters, catheters, replacement and anticoagulation solutions.

New intake of critically ill survivors with severe AKI into ESKD dialysis programs will be reviewed on a quarterly and yearly basis to determine any changes relevant to use of this resource to the Alberta healthcare system. We will ensure that any changes in intakes reflect acute KRT initiations based on adherence to best-evidence practices.

Data will be collected on patient characteristics: (i.e., demographics, type of admission [medical, surgical, trauma]), clinical status (i.e., comorbid diseases including chronic kidney disease, primary diagnosis), acuity (i.e., APACHE II, SOFA, CFS), ICU treatment (i.e., duration of renal replacement therapy, mechanical ventilation, vasoactive therapy), ICU and hospital lengths of stay, and outcomes (i.e., renal recovery and mortality); and KRT-associated resource data: (i.e., filter use, prescription/dose, machine alarms/down time, anticoagulation, re-hospitalizations, progression of renal disease). Data variables to be captured are summarized in Table 4.

**Table 4 Tab4:** Data variables

Data Variable	Description
ICU location	admission ICU
Age	years
Sex:	M/F
Weight	kg
Date of Hospital Admission	dd/mm/yyyy
Date of ICU Admission (dd/mm/yyyy):	dd/mm/yyyy
Admission class	med/surg/neuro/trauma
ICU discharge location	unit/hospital
ICU Admission Diagnosis – cardiovascular, respiratory, gastrointestinal, genitourinary/renal, endocrinological/metabolic, neurological, trauma, burn, sepsis, surgery	yes/no
Co-morbidities – AIDS, chronic RRT, chronic heart failure, respiratory insufficiency, cirrhosis, diabetes mellitus, hepatic failure, immune suppression, leukemia, lymphoma, metastatic cancer, coronary artery disease	yes/no
Clinical Frailty Scale	number

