APACHE II Score	number
SOFA score	number
Invasive/non-invasive ventilation	hrs/min
Vasopressors (include type)	hrs/min
CRRT/IHD/SLED	hrs/min
Cumulative daily fluid balance prior to RRT	mls
Creatinine, urea, pH, bicarbonate, potassium on day of RRT initiation	result
Renal Recovery at ICU Discharge	y/n - IHD
Renal Recovery at Hospital Discharge	y/n – IHD/PD
Renal Recovery at 6 Months	y/n - IHD/PD
ICU Mortality	A/D
Hospital Mortality	A/D
6-month Mortality	A/D
ICU length of Stay	days
Hospital Length of Stay	days
Number of admissions to site	aggregate
Patient days	aggregate
Ventilator days	aggregate
RRT days	Days CRRT/IHD/SLED
CRRT and IRRT data - filter life, reasons for retiring filters, treatment time lost, prescription/dose, machine alarms, machine down times, type of coagulation, blood flow rates, filtration fraction, adverse events, solute clearance, ultrafiltration realized	aggregate
Economic data - cost of filters, fluids, anticoagulation medications, RRT catheters, patient life-years gained, quality of life adjusted years (QUALY), re-hospitalizations, recurrence/chronic RRT, health care provider related costs	aggregate
QOL and PROMs	aggregate

Data sources will include multiple Alberta Health Services administrative databases, the Nephrology Information System (NIS) and the Patient Based Renal Information System (PARIS) (Supplementary Table 1) [20, 21].

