### Statistical analyses

#### Health outcome measures

The patients’ characteristics and the target clinic outcomes in the baseline and intervention periods will be summarized. Mean (SD) and/or median (IQR) will be used for continuous variable; frequency will be used for categorical variables. To compare pre- and post-intervention difference, *p*-values will be provided by t-test (for normally distributed variables), non-parametric Wilcoxon tests (for non-normally distributed variables) or Chi-square test (for categorical variables). Interrupted time series (ITS) analyses will use autoregressive integrated moving average (ARIMA) models to determine changes in the KPI performance following the implementation of the acute KRT pathway.

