#### Healthcare system costs analysis

The primary health economic evaluation will be a within-study analysis of the cost-effectiveness of the Dialyzing Wisely program. Subject to available resources we will consider additional model-based analyses of Dialyzing Wisely over a longer time horizon.

The within-study analysis will be conducted on resource use and outcomes occurring during the study period. It will include total quarterly acute KRT-associated costs for each specific ICU following the implementation of KPI reporting. The cost analysis will include 1) utilization costs of CKRT filters, CKRT fluids, KRT anticoagulation (if any),and KRT catheters. Costs will be calculated in part using acute KRT process measures captured by our acute KRT KPIs.

We will also conduct an analysis of healthcare systems costs including those associated with total ICU and hospital stay and ongoing new ESKD costs (i.e., long-term, maintenance dialysis costs, total healthcare costs. Healthcare system costs will be reported as costs of acute KRT in ICU as a proportion of total ICU costs per quarter. Modeling analysis will capture costs to the health service, social care providers and patients so as to provide cost estimates from a societal perspective. We will determine models for averted and delayed acute KRT and averted new end-stage kidney disease requiring chronic dialysis based on observed changes in practice based on prescriber reports and adherence to best-evidence. Results will be reported as the incremental net benefit and incremental cost-effectiveness ratios. Uncertainty will be captured in the analyses through probabilistic sensitivity analysis and reported using cost- effectiveness acceptability curves, showing the likelihood the intervention will be cost-effective over a range of values of willingness-to-pay thresholds for specific outcomes.

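### Mortality, 90-day KRT dependence and length of stay are compared before and after among KRT recipients, a group whose membership the pathway is meant to change; the resulting selection bias has no known direction

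*Protocol article*

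**What the plan says.** Under Population and eligibility, the Protocol article admits ICU patients who receive acute KRT: "The inclusion criteria will be critically ill patients (i.e., adults and children) receiving acute KRT as part of their routine ICU care". It adds "No exclusion criteria will be applied" and names no other cohort.

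The second of the two interventions is "Provision of individualized prescriber and program reports for acute KRT initiation patterns". The Prescriber reporting section lists among the report contents "acute KRT initiations based on conventional indications (i.e., hyperkalemia, acidosis, metabolic status, oxygenation status and cumulative fluid status) termed ‘appropriate initiations", and Table 2 sets potassium, pH, bicarbonate, oxygenation and fluid-balance benchmarks for initiation. The Healthcare system costs analysis section states: "We will determine models for averted and delayed acute KRT and averted new end-stage kidney disease requiring chronic dialysis".

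Secondary outcomes include ICU and 90-day mortality, the rate of KRT dependence at 90 days, and ICU and hospital stay. No denominator is given for the dependence rate. Under Health outcome measures the comparison reads "To compare pre- and post-intervention difference, *p*-values will be provided by t-test (for normally distributed variables", with rank and chi-square tests for other variable types and ARIMA interrupted time-series models alongside. The one severity adjustment, under Data management, applies to initiations. Table 4 lists APACHE II and SOFA, and "Number of admissions to site" as an aggregate. The primary outcomes include a count of patients entering maintenance KRT programs.

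**The concern.** Receiving acute KRT is the entry event, and the prescriber reports are designed to act on that event. A patient who would have been started before the pathway, and who now gets through the ICU stay without KRT, is in the baseline cohort but has no counterpart in the intervention cohort. The two groups then differ by selection even if nobody's outcome has changed.

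Nothing stated in the article removes this. The unadjusted tests compare the two selected groups directly. ARIMA handles trend and autocorrelation, but not a change in case mix that the intervention causes and that arrives with it. Averted KRT is considered only in the economic modelling.

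At stake is how the patient outcomes are read. The Methods/design section says the impact of the intervention will be measured through outcomes such as mortality, stay and renal recovery. A working pathway could be reported as harmful, or an ineffective one as beneficial.

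**Working it through.** The article states no figure on this point, so there is nothing to reproduce. The check asks how far recipient-only rates can move when no patient's outcome changes.

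**Inputs from the article.** 1278 patients started acute KRT in 2019, described as 5–8% of the critically ill population (Acute KRT in Alberta). Accelerated start carries a 74% relative increase in 90-day dependence, a ratio of 1.74 (Time of KRT initiation).

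**Assumed inputs.** The share of starts averted, f, is 10% to 40%. Mortality is 45% in remaining recipients and 25% to 55% in averted patients. Dependence per KRT starter is 8% in remaining recipients and 2% to 12% in averted patients.

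**Formula.** Recipient rate before = (1 − f) × r_remaining + f × r_averted. Recipient rate after = r_remaining. For example, with f = 30% and averted mortality of 25%: before = 0.70 × 45% + 0.30 × 25% = 39.0%; after = 45.0%.

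**Mortality, no individual outcome changed.** The last column is the chance that the artefact alone reaches two-sided p < 0.05, with 1278 patients before and (1 − f) × 1278 after, ignoring clustering and trend.

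| Mortality if averted | Recipient rate, f = 10% | Recipient rate, f = 40% | Chance of significance, f = 10% to 40% |
|---|---|---|---|
| 25% | 43.0% → 45.0% | 37.0% → 45.0% | 0.17 to 0.95 |
| 35% | 44.0% → 45.0% | 41.0% → 45.0% | 0.07 to 0.43 |
| 45% | no shift | no shift | no artefact |
| 55% | 46.0% → 45.0% | 49.0% → 45.0% | 0.07 to 0.42 (false improvement) |

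In the 25% row the intermediate chances are 0.49 at f = 20% and 0.80 at f = 30%.

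**Dependence, same method.** With 5% in averted patients, the recipient rate goes from 7.7% to 8.0% (f = 10%) up to 6.8% to 8.0% (f = 40%). With 12% it goes from 8.4% to 8.0% up to 9.6% to 8.0%, a false improvement.

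**A case where the pathway helps and recipient rates worsen.** Take 100 baseline recipients. Forty start without a criterion (30% mortality, 8% of survivors dependent) and 60 with one (55%, 20%).
- Before: deaths 12 + 33 = 45, so 45.0%. Survivors 28 + 27 = 55. Dependent 2.24 + 5.40 = 7.64, and 7.64/55 = 13.9%.
- Avert 20 of the 40, with their survival unchanged and their dependence prevented. Among 80 recipients: deaths 6 + 33 = 39, so 48.8%. Survivors 14 + 27 = 41. Dependent 1.12 + 5.40 = 6.52, and 6.52/41 = 15.9%.

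Deaths among the 100 are unchanged and dependent patients fall by 15%, yet both recipient rates rise.

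**The same case with two inputs altered.** Use 12% instead of 8%, and let the 20 non-criterion patients still treated be delayed starts whose risk is divided by 1.74.
- Before: 3.36 + 5.40 = 8.76, and 8.76/55 = 15.9%.
- After: 14 × 0.12/1.74 = 0.97; 0.97 + 5.40 = 6.37, and 6.37/41 = 15.5%.

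The dependence rate now falls.

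**Fixed denominator for dependence.** Let f = 30%, with 8% dependence in remaining patients and 5% in averted patients falling to 5%/1.74 = 2.9%. New dependent patients go from 91 to 83 among the same 1278 candidates, while the recipient rate rises from 7.1% to 8.0%. If the 5–8% refers to admissions, these number 1278/0.08 = 15,975 to 1278/0.05 = 25,560. The rate per 1,000 admissions then falls from 5.7 to 5.2, or from 3.6 to 3.2, in step with the count.

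**The case against.** A reader might infer that the bias runs against the pathway, because patients started without hyperkalemia, acidosis, hypoxemia or fluid overload ought to be less ill. That is plausible, but the article reports no outcomes for such patients. The working shows that the shift vanishes at equal risk and reverses at higher risk.

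A reader might also infer that the trial's main patient-relevant result is compromised. It is not. The outcomes affected are secondary, and the primary count of patients entering maintenance KRT has no recipient denominator. A falling count beside a rising recipient-only rate is no contradiction, and the number of initiations is also to be reported, so the shrinking cohort would be visible.

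A further objection is that denominators and covariate adjustment are commonly left to an analysis plan, and none is shown. This stands in part: the article gives no denominator for the dependence rate, and its absence is not the finding. The finding is the restriction of the population to recipients, which the article does fix. Adjustment among recipients cannot restore patients who never enter the cohort. It removes the bias only if the measured covariates capture everything that drives the decision to start.

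The last objection concerns the remedy, and it stands. Site admissions are listed only as an aggregate, and the article does not show that deaths or stays of non-recipients are collected. Dividing recipient deaths by admissions would add a new bias: an averted patient who dies would leave the numerator, giving a false benefit.

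**Conclusion.** The concern holds as a moderate point on the secondary outcomes. Before-after comparisons of mortality, 90-day dependence and stay among KRT recipients are selected by the intervention, and no stated analysis corrects for that. Under the assumed ranges the mortality artefact runs from +8 to −4 percentage points, with zero at equal risk. At the upper end it would very probably be declared significant with one year of patients before and a correspondingly smaller year after. These sizes rest on assumed shares averted and assumed risks. The mechanism needs only that some starts are averted and that those patients differ in risk from the rest. The argument is most direct for mortality; for dependence and stay the shift depends on how averted patients differ on those outcomes in particular. The documents do not support a stated direction, and the primary count of patients entering maintenance KRT should stay as it is.

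**What to change.** 1. Report 90-day KRT dependence as new dependent patients per 1,000 ICU admissions per ICU-period, using the site admissions already in Table 4, with absolute counts beside the rate. Take the numerator from intake of critically ill survivors with severe AKI into dialysis programs, which Data management already plans to review. A patient who becomes dependent without having had acute KRT is then still counted.
2. Label recipient-only comparisons of mortality, dependence and length of stay as descriptive. Show them with the number of initiations and the case mix of recipients (APACHE II, SOFA) in each period.
3. Establish whether the administrative databases supply outcomes for patients who did not receive KRT. Only if they do, analyse mortality and stay in all ICU patients with severe AKI, or in all ICU admissions, whether or not they received KRT. Do not divide recipient deaths by admissions.

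The first two changes use variables already listed and cost little beyond attributing dialysis intake to the ICU of origin. The third may need a further data extract. With only 5–8% of critically ill patients receiving KRT, effects on mortality and stay would be heavily diluted in an all-admission analysis; a severe-AKI cohort, where it can be identified, would limit that.
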